##### Recruitment of Participants 

Similar recruitment strategies will be used to recruit participants for the pilot study as those used for the co-creation trajectories. (See Recruitment of Participants Part in Section 2.2.1) If the recruitment strategy of solely using schools is insufficient to obtain the required number of participants, an additional strategy will be used: launching a call for grandparents via Ghent University Research Consortium for Aging Young (GRAY) and its partners (e.g., the Flemish Council on Aging). GRAY is an interdisciplinary research consortium on healthy aging. Eligible grandparents will receive an information letter and fill in contact information for their grandchildren and themselves (both must be able to participate) to be returned to the researchers. A researcher will call the grandchildren’s parents and grandparents to probe for sociodemographic characteristics and inclusion criteria. There are no specific restrictions regarding age or gender in the pilot study, which differs from the co-creation sessions, where limits are placed on the numbers of younger and older children and there will be a good mix between boys and girls and grandmothers and grandfathers. 

##### Content of the Sessions

A total of about six sessions per group (e.g., one session per week) will take place over the course of six weeks (depending on input from the co-creation sessions) at a preferred time during the week. Group 1 will engage in the intergenerational movement program; Group 2 will engage in the cognitively enriched intergenerational movement program. The duration and content of the sessions will depend on the needs and preferences of the target group and the intervention goals that were set during the co-creation sessions (e.g., movement activities: balancing on a bench, relays, ballgames; and cognitively enriched movement activities; walking/running games, searching for objects in the environment, coordinative exercises while counting). According to the recent PA guidelines of the WHO for children and older adults, researchers will integrate coordination, balance, mobility, and strength into the sessions.

##### Measurements

Process Evaluation

After each session, a short questionnaire will be administered to probe for the thoughts and feelings of the grandchildren and grandparents regarding attractiveness and feasibility during the activities and to determine which kinds of topics or activities they prefer the most (e.g., games, exercises, activities with one’s own grandchild or also with the other grandchildren). The Physical Activity Enjoyment Scale (PACES) will be used to assess the level of enjoyment among grandparents. This short, validated questionnaire for older adults includes eight items that will assess how much fun the grandparents experienced during the (cognitively enriched) movement activities [62]. The use of emoji questionnaires with younger children can measure their emotional responses and can also help them to understand abstract concepts and express themselves. Therefore, smileys will be used to express the level of enjoyment in children [63]. After the six sessions, an additional, self-administered questionnaire will evaluate participation in the sessions, recruitment strategy, group size, age, and the clarity of the questionnaires that have been administered after the sessions. A focus group with at least three stakeholders (e.g., MOEV, Gezinssport Vlaanderen, and Sportwerk Vlaanderen) will be organized to share ideas and to receive expertise to finetune the activities of the preliminary movement program. An observer will write down the most interesting points. MOEV is an abbreviation for Motivatie (Motivation), Ondersteuning (Support), Expertise (Expertise) and Vernieuwing—Vlaanderen—Vitaliteit (Renewal—Flanders—Vitality). MOEV is an organization that motivates and supports schools in the development of their exercise and sports policies; the aim is that toddlers, primary school children, and adolescents will have fun by being physically active.

Evaluating the use of outcome measures for the RCT

To objectively measure PA in the grandchildren and grandparents, the Axivity AX3 accelerometers or the ActiGraph wGT3X-BT will be used. Half of the group doing the intergenerational movement program will wear the first accelerometer; the other half will wear the second one. During the cognitively enriched sessions, half of the group will also wear the first one; the others will wear the second one. The most feasible, practical, and useable of the accelerometers will be chosen to be used as a measure in the RCT. These accelerometers will be used in combination with a seven-day diary (pre- and post-follow-up) to subjectively measure PA, and they will be worn during certain sessions. More details about the measurement instruments are described below in Outcome Measures part of Section 2.2.3.

To objectively measure cognitive functioning in the grandchildren and grandparents, CANTAB tests will be used. The purpose will be to assess the feasibility, usability, and practicality of the test battery. The pilot study will be used to make a final selection of which cognitive tests to include in the RCT and decide on the ideal total duration of the cognitive testing procedure (e.g., +/− 40 min) based on practicality and discriminating power. More details are described in Outcome Measures part of Section 2.2.3.

To measure psychosocial well-being in the grandchildren and grandparents, several questionnaires will be administered. The preferred mode of delivery (online or paper-and-pencil questionnaires), the number of questionnaires, and the total duration of completing the questionnaires will be evaluated. Potential unclarities or difficulties when completing the questionnaires will be detected in order to improve this in the actual RCT. More details are described below in Outcome Measures part of Section 2.2.3.

Furthermore, participants will be asked for input and feedback on the measures and measurement instruments using a short questionnaire.

##### Achieving the Intervention Goals

Depending on the findings that emerge from the co-creation sessions, a gadget or material (e.g., stickers, magnets, eyecatchers, or posters) can be developed to optimally achieve the intervention goals. A self-administered questionnaire will assess whether these program materials are perceived as positive and supportive to achieving the intervention goals.

##### Data Analysis

The answers on the open-ended questions in the questionnaires will be coded using content analysis. The answers on the Likert scale questions in the questionnaires will be coded using SPSS [64]. Multilevel linear analysis will be used to measure the effects of co-PA.

#### 2.2.3. Randomized Controlled Trial (RCT)

The RCT will be conducted subsequent to the pilot study so as to measure the effects of the two different programs on the outcomes of PA, cognitive functioning, psychosocial well-being, and quality of the family relationship in the grandchildren and grandparents and to evaluate the process of the study. The RCT will consist of two intervention groups, Arm 1: Intergenerational PA and Arm 2: Cognitively enriched intergenerational PA, and one control group. Intervention Group 1 will receive the intergenerational movement program, Intervention Group 2 will receive the cognitively enriched intergenerational movement program, and the control group will receive no intervention. The pre- (before the start of the sessions), post- (after 24 weeks) and follow-up (after 36 weeks) outcome measures of PA, cognitive functioning, psychosocial well-being, and quality of the family relationship will be compared between Group 1 and the control group, between Group 2 and the control group, and between Groups 1 and 2. An overview of the RCT is shown in Figure 5.

##### Participants and Sample Size

The same inclusion criteria will be used for the RCT as in the co-creation trajectories and the pilot study (i.e., speaking Dutch; having at least one grandparent or grandchild; and having no serious physical, cognitive, or psychological health problems). Based on effect sizes of intergenerational programs of children and older adults, an effect size of 0.15 will be intended for the outcomes of PA, cognitive functioning, psychosocial well-being, and quality of the family relationship [65]. The required sample size has been calculated using the software GPower 3.1.9.7 (Universität Düsseldorf, Düsseldorf, Germany) [60]. The sample calculation will be based on 80% power to detect a significant difference in PA, cognitive functioning, psychosocial well-being, and quality of the family relationship between groups and over time. Significance level alpha 0.05, having 3 groups (2 intervention groups and 1 control group) and 3 measurements (pre-, post-, and follow-up). A priori power analysis for the RCT suggests a total sample size of around 45 dyads (*n* = 90 grandchildren and grandparents). Assuming an attrition rate of 20% [61], a total sample size of 54 dyads (*n* = 108 grandchildren and grandparents) will be required for the 3 groups. (Each group consists of 36 participants: 18 grandchildren and 18 grandparents). See Figure 4.

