##### Participants and Sample Size

Similar inclusion criteria will be used to recruit participants for the pilot study as those used for the co-creation trajectories. (See Participants and Sample Size Part in Section 2.2.1) The required sample size for a pilot study is between 30 and 50 participants [59]. Therefore, and also taking into account a group size where safety can be guaranteed, two groups of 12 dyads will be recruited (i.e., in total, about 24 grandchildren and 24 grandparents; 12 grandchildren and 12 grandparents per group, including the participants of the co-creation sessions), assuming an attrition rate of 30% (7 dyads) [61], and guaranteeing a sufficiently large group size for the sessions. A projected attrition rate of 30% instead of 20% has been chosen because we have taken into account that, if one grandchild or grandparent drops out, this implies that the whole dyad will be excluded from the study. Therefore, 2 groups of 12 dyads will be recruited (a total of about 24 grandchildren and 24 grandparents). (See Figure 4).

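### The RCT's 20% attrition allowance is computed as 45 × 1.2 = 54 dyads, which leaves about 43 dyads rather than 45 and covers only 16.7% loss (a minor error)

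*Protocol article*

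**What the plan says.** Section 2.2.3 of the protocol article (Participants and Sample Size) describes a G*Power calculation. On effect size it says that "an effect size of 0.15 will be intended for the outcomes of PA" and the other outcomes. On power: "The sample calculation will be based on 80% power to detect a significant difference in PA" and the other outcomes between groups and over time. The remaining stated inputs are: "Significance level alpha 0.05, having 3 groups (2 intervention groups and 1 control group) and 3 measurements".

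The result is given as: "A priori power analysis for the RCT suggests a total sample size of around 45 dyads", equated with 90 people. The attrition step follows at once: "Assuming an attrition rate of 20% [61], a total sample size of 54 dyads", equated with 108 people. The split is then stated: "Each group consists of 36 participants: 18 grandchildren and 18 grandparents". The inflation formula is not given. Figure 4 is cited for the numbers but is not reproduced in the text available here.

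The pilot study (section 2.2.2, Participants and Sample Size) shows how the article uses an attrition rate. It plans 24 recruited dyads, "assuming an attrition rate of 30% (7 dyads"), and explains that "if one grandchild or grandparent drops out, this implies that the whole dyad will be excluded from the study".

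**The concern.** An attrition allowance is meant to ensure that the required number remains after the expected loss. That calls for dividing the requirement by the retained fraction. Multiplying by one plus the loss rate always falls short, because the loss applies to the larger, recruited number. Here the paragraph states a requirement, a loss rate and a target, and the three do not fit together. The 54 dyads are the trial's recruitment target, so a reader would take them to deliver the required sample at 20% loss, and they do not.

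**Working it through.** **Inputs.** From section 2.2.3: 45 dyads (90 people) required; 20% attrition; target 54 dyads (108 people), 18 dyads per group; effect size 0.15; alpha 0.05; power 80%; 3 groups; 3 measurements.

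**1. Reproducing the target.**
- Requirement × (1 + loss): 45 × 1.20 = 54 and 90 × 1.20 = 108. Both match exactly.
- Requirement ÷ (1 − loss): 45/0.80 = 56.25 and 90/0.80 = 112.5. Neither matches.

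The 1.2 multiplier is inferred from the numbers, since the formula is not printed.

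**2. What the target delivers at 20% loss.**
- 54 × 0.80 = 43.2 dyads, or 108 × 0.80 = 86.4 people.
- Shortfall: 45 − 43.2 = 1.8 dyads, about 0.6 per group.
- Loss that 54 dyads can absorb: (54 − 45)/54 = 9/54 = 16.7%.

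**3. Whether attrition means a share of those recruited.** In the pilot, 30% × 24 recruited dyads = 7.2, printed as 7. The article's own usage is a share of those recruited, so step 2 applies the rate as the article does.

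**4. Target consistent with 45 dyads and 20% loss.** 45/0.80 = 56.25, which rounds up to 57, a multiple of three: 19 dyads per group, 114 people. Check: 57 × 0.80 = 45.6, which meets 45.

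**5. Effect on power.** The article does not state the effect-size metric, the test, the correlation among measurements, the nonsphericity correction or the unit of analysis. The following are therefore assumptions: Cohen's f = 0.15, the within-between interaction in a repeated-measures ANOVA, epsilon = 1, and individuals as independent units. With N people, m = 3 measurements, k = 3 groups and correlation ρ:
- noncentrality λ = f² × N × m/(1 − ρ)
- degrees of freedom (k − 1)(m − 1) = 4 and (N − k)(m − 1)

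At ρ = 0.5, 80% power needs N = 91, close to the printed 90, so this set of assumptions is plausible. It gives:

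| People | λ | Power |
|---|---|---|
| 90 (the stated requirement) | 12.15 | 79.6% |
| 86.4 (54 dyads less 20%) | 11.66 | 77.6% |
| 91.2 (57 dyads less 20%) | 12.31 | 80.2% |

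The shortfall costs 79.6 − 77.6 = about 2 percentage points.

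**6. Sensitivity to the assumed correlation.** At 86.4 people, power is 68.8% at ρ = 0.4, 77.6% at 0.5, 82.4% at 0.55 and 87.1% at 0.6. This unstated input moves power far more than the 3.6 people at issue.

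**The case against.** Four points can be made for leaving the figure alone.

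**The base is approximate.** The article says around 45, and the gap is under two dyads in total. This stands as an argument about severity. It does not reconcile the numbers, because 54 and 108 are exact multiples of 45 and 90, so the base was used as exactly 45.

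**The 20% might mean over-recruitment relative to 45.** This does not stand. The article calls it an attrition rate, and the pilot applies that term to those recruited.

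**Dropouts may still contribute data.** The RCT analysis is a multilevel linear model over three measurements, which can use partial data from people who leave after baseline. The rule that a whole dyad is excluded is stated for the pilot and not repeated for the RCT. This stands: 43.2 is a count of complete dyads, and the power at 86.4 people is a worst case if partial data are kept.

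**Other inputs matter more.** The assumed correlation is one. The attrition rate is another: the pilot section explains 30% instead of 20% by the loss of whole dyads, yet the RCT uses 20%. At 30%, 54 dyads would leave 54 × 0.70 = 37.8. This also stands, and it means that 57 is right only given 45 dyads and 20% loss.

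A reader might infer that the plan's own calculation shows the trial to be underpowered, or that 57 is the one correct target. The documents support neither. The power values rest on assumptions the article does not state, and under them the base of 90 people is itself already slightly under 80%.

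**Conclusion.** The target is wrong as written; severity is minor. From the printed figures alone, 54 dyads less 20% leave about 43 dyads (86 people) against the roughly 45 (90 people) required, and 54 covers 16.7% loss rather than 20%. Nothing elsewhere in the article repairs this.

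The power consequence is conditional. It is about two percentage points for completers, under the assumptions listed in the working, and the absolute level cannot be fixed without the correlation used. The error alters neither the design nor the analysis, and does not by itself show that the trial is materially underpowered.

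**What to change.** Restate the sentence in section 2.2.3 in one of two ways.

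1. Keep 54 dyads (18 per group, 108 people) and say that this allows for 16.7% attrition; or say that at 20% attrition about 43 complete dyads are expected, with power slightly under 80%. The cost is one reworded sentence and a slightly less favourable statement.
2. Keep 45 required and 20% loss, and correct the target to 57 dyads (19 per group, 114 people). The cost is three more dyads, one per group.

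Whichever is chosen, check that Figure 4 shows the same number. If a power value is quoted, state the effect-size metric, correlation, epsilon and unit of analysis with it.

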##### Recruitment of Participants

According to the evaluation of the recruitment strategy of the co-creation sessions and the pilot study, the best way to recruit the target population will be chosen based on convenience sampling. The strategies and procedures for the recruitment are described above in the discussion of the recruitment for the co-creation trajectories and pilot study. The first strategy will be the recruitment of grandchildren and their grandparents via schools in (the neighborhood of) Ghent. The second strategy will be via GRAY and their partners. A combination of both strategies is also possible if needed to achieve the desired number of participants.

##### Content of the Sessions

A total of 12 (or 24) sessions (1–2 session(s) every (1 –2) week(s) per group will take place over 24 weeks at a preferred time during the week (e.g., Wednesday afternoon, Tuesday evening, Thursday evening, etc.). All of this will depend on the preferences of the grandchildren and grandparents. Arm 1 and Arm 2 will receive different sessions during the same week. Arm 1 will receive only movement activities, while Arm 2 will receive cognitively enriched movement activities. The content of the sessions will have been refined during and after the pilot study to best meet the needs and preferences of the grandchildren and grandparents (e.g., duration, topics, and format). After the follow-up measurements, the intervention groups will also receive a brochure detailing (cognitively enriched) movement activities that they can perform at home to achieve a long-term effect.

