
### 4.2. Potential Strengths and Limitations of This Study

A first potential strength of this study includes the experimental and longitudinal design. A second potential strength is the use of the Behaviour Change Wheel in combination with a co-creation approach in which end-users and stakeholders will collaborate in the development of the movement program. This may lead to a more effective intervention, and it will also prevent drop-out because the needs and preferences of the grandchildren and grandparents will be taken into account [51,52,53,54]. In addition, organizations working with children and older adults (stakeholders) will be asked to offer information about the usefulness, attractiveness, and feasibility of the movement activities (i.e., a bottom-up instead of a top-down approach, which means that researchers base the research upon the end-users, rather than upon a general theory or idea based on findings in the literature) [77]. A last potential strength is that PA and cognitive functioning will be measured objectively through accelerometry and CANTAB tests, while self-report measures (e.g., questionnaires and diaries) can lead to response and recall biases [78].

A first potential limitation of this study includes the lack of blinding, as the researcher will be involved in the data collection and analysis. Therefore, a strict protocol has been created so as to reduce this limitation as much as possible. A second potential limitation includes the recruitment strategy. Convenience sampling will be used for the co-creation sessions, the pilot study, and the RCT. It is therefore expected that grandchildren and grandparents who are already more physically active and motivated to move will be interested participating. However, this will be taken into account during the recruitment by mentioning that the levels will be attainable for everyone and that the focus will not only be on the movement activities, but also on creating a pleasant atmosphere by making the activities fun, attractive, and feasible for the target group.

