	**WHEN and HOW MUCH**		
8.	Grandchildren and their grandparents will participate in a cognitively enriched movement program, which will be developed by themselves together with the researchers (co-creation). The preferences and needs of the target group will determine what the program will look like. A total of 12 (or 24) sessions (one/two session(s) every (two) week(s) per group will take place during 24 weeks on a preferred time during the week (e.g., Wednesday afternoon, Tuesday evening, Thursday evening…). There will be two arms, arm 1 will receive only movement activities, arm 2 will receive cognitively enriched movement activities. The content of the sessions (duration, topics, format, materials) will be refined after the pilot study. Intervention groups will receive a brochure with (cognitively enriched) movement activities they can perform at home after the follow-up measurement to create a long-term effect. This part of the checklist will be refined after the pilot study, when there is more information available about the movement sessions.	p. 16	_____________

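### The take-home brochure goes only to the intervention arms; giving it to controls after week 36 is a cheap change that could support control-arm retention

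*Protocol article*

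**What the plan says.** Under Content of the Sessions in Section 2.2.3, the article states: "After the follow-up measurements, the intervention groups will also receive a brochure detailing (cognitively enriched) movement activities that they can perform at home". The stated purpose is a long-term effect. Item 8 of the TIDieR checklist in Appendix A repeats the rule and again names only the intervention arms: "Intervention groups will receive a brochure with (cognitively enriched) movement activities they can perform at home after the follow-up measurement".

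For the comparator, Section 2.2.3 says that "the control group will receive no intervention", and the overview in Section 2.1 agrees. No wait-list, delayed programme or other later offer to controls is described. All groups are compared on "post- (after 24 weeks) and follow-up (after 36 weeks) outcome measures" as well as the baseline measures.

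Section 4.2 expects that "grandchildren and grandparents who are already more physically active and motivated to move will be interested participating". The same section, and Section 2.1.2, argue that co-creation limits drop-out because the programme is shaped to participants' needs. Attrition enters the sample size as one overall figure: "Assuming an attrition rate of 20" per cent, with 18 dyads planned per arm.

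**The concern.** Families are recruited for a joint movement programme, and one third are then allocated to nothing. Section 2.2.5 says participants are told the design and may leave at any time, and a no-intervention arm cannot be masked, so controls know what they are missing. They are still asked for accelerometer weeks, diaries, CANTAB sittings and questionnaires at three time points, from both a child and a grandparent. The one retention mechanism the article argues for operates through programme content that controls never see.

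Withdrawal could therefore be higher among controls. If those who leave differ on the outcome from those who stay, Arm 1 against control and Arm 2 against control could both be biased. Section 4.2 lists lack of blinding and the recruitment strategy as limitations, but not differential withdrawal. Keeping the brochure from controls after week 36 protects no comparison, because measurement has finished by then.

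**Working it through.** **The plan's own figures.** From Participants and Sample Size in Section 2.2.3: "The sample calculation will be based on 80% power to detect a significant difference", and "Significance level alpha 0.05, having 3 groups (2 intervention groups and 1 control group) and 3 measurements", with an effect size of 0.15. The article names neither the effect-size index nor the correlation between measurements. I took 0.15 as Cohen's f and assumed a correlation of 0.5 and sphericity, for a repeated-measures within-between interaction:

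- Noncentrality = f² × N × m / (1 − ρ) = 0.0225 × 90 × 3 / 0.5 = 12.15
- Degrees of freedom = (3 − 1)(3 − 1) = 4 and (90 − 3)(3 − 1) = 174
- Power = 0.796, close to the stated 80%

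The stated 90 individuals (45 dyads) is thus roughly reproduced with 0.15 read as f. The 54 dyads equal 45 × 1.2. A 20% loss leaves 54 × 0.8 = 43.2 dyads, or 14.4 per arm if loss is even. Whether 54 is the right inflation of 45 is a separate matter.

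**Assumed loss patterns.** The documents give none by arm. Both patterns below keep the stated 20% overall, with 18 dyads randomised per arm.

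| Loss: Arm 1 / Arm 2 / control | Average | Dyads left per active arm | Dyads left, control |
|---|---|---|---|
| 20 / 20 / 20% | 20% | 14.4 | 14.4 |
| 15 / 15 / 30% | 60/3 = 20% | 18 × 0.85 = 15.3 | 18 × 0.70 = 12.6 |
| 10 / 10 / 40% | 60/3 = 20% | 18 × 0.90 = 16.2 | 18 × 0.60 = 10.8 |

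**Precision.** The standard error of a control contrast is proportional to √(1/n_active + 1/n_control).

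- Even loss: √(2/14.4) = 0.373
- 15% v 30%: √(1/15.3 + 1/12.6) = 0.380, ratio 1.021
- 10% v 40%: √(1/16.2 + 1/10.8) = 0.393, ratio 1.054

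The precision loss is about 2% to 5%, which is small.

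**Bias in a completers comparison.** Suppose leavers differ from stayers by D standard deviations, in the same direction in every arm. An arm that loses a fraction d then has its completer mean displaced by d × D. The contrast is biased by (d_control − d_active) × D.

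| Gap in loss | D = 0.2 SD | D = 0.5 SD |
|---|---|---|
| 0.30 − 0.15 = 0.15 | 0.03 SD | 0.075 SD |
| 0.40 − 0.10 = 0.30 | 0.06 SD | 0.15 SD |

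The gap between Arms 1 and 2 is zero in both patterns, so that contrast is unaffected.

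**The case against.** **Direction.** The documents do not say which arm will lose more. The active arms carry 12 or 24 sessions in Ghent over 24 weeks, plus an evaluation after each session, and could lose as many families or more. This stands: higher loss among controls is an inference, and if the gap ran the other way the bias would change sign and a brochure for controls would not address it.

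**Silence.** A reader might infer that nothing at all keeps controls in the study. The article does not support that. It is condensed, the information letter is not shown, and both places that mention the brochure describe the intervention, where control-arm arrangements would not be expected. What remains is narrower: the recipients of the brochure are stated twice, and controls are not among them either time.

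**Effect of a brochure.** A reader might also infer that promising the brochure would cut withdrawal. Nothing in the documents shows this. The article gives the brochure a different purpose, and a leaflet delivered some 36 weeks later may be a weak incentive. That it could help is as far as one can go.

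**Analysis.** The bias formula is for a raw completers comparison, whereas Data Analysis in Section 2.2.3 plans a multilevel linear model. Such a model can use partial records and lessens bias where loss depends on observed data. It does not remove bias where loss depends on unobserved outcomes.

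**Conclusion.** The point holds as a modest design improvement. The article restricts the brochure to the intervention arms, there is a plausible route to higher withdrawal among controls, and the restriction protects no comparison. No stated figure in the plan is wrong on this account, and a single overall attrition rate is ordinary practice.

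The bias range of 0.03 to 0.15 SD rests on assumed loss rates, an assumed difference between leavers and stayers, and a completers analysis. Its upper end needs the most extreme pair of those inputs.

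Two larger conclusions may tempt a reader. One is that the bias could equal the whole planned effect, because both figures read 0.15. That probably mixes scales: the sample size is roughly reproduced when 0.15 is Cohen's f, which is not a mean difference in SD units. The other is that every effect claim is exposed. Section 2.2.3 also compares Groups 1 and 2, and the hypothesis in Section 3 about cognitive enrichment draws on that contrast, which does not involve controls.

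**What to change.** Amend Content of the Sessions in Section 2.2.3 and item 8 of the TIDieR checklist so that all three arms receive the brochure once their own week-36 measurement, including the accelerometer week, is complete. State this in the information letter that every dyad reads before randomisation, so that the offer is known to all arms alike and could give controls a reason to stay.

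The cost is printing for 18 more dyads and one sentence in the letter. The brochure is being produced anyway, and since it arrives after the last measurement it cannot affect any planned contrast.
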